**Fig. 2 Fig2:**
[figure not shown]
Eligibility and assessment timetable

Psychometric variables, including sociodemographic and diagnostic measures described above, that are pertinent to the unique combination of MUD, MIGT, and oxytocin administration, will be collected during the initial screening visit. Additional variables will include the following: The Experiences in Close Relationship Scale – Short Form (ECR-S) [80], which is a 12-item measure of the construct of adult attachment, resulting in scores for attachment anxiety and attachment avoidance. For this study, we will substitute the term “romantic” for “intimate,” which we defined as “emotional closeness, including close family relationships and/or romantic relationships.” The Adverse Childhood Experiences (ACE) Questionnaire [81] is a 10-item measure of childhood experiences of abuse and neglect. ACE scores have a strong graded relationship to the risk of developing and maintaining substance use disorders [82] and modify the relationship between intranasally administered oxytocin and cortisol reactivity in stimulant users [31]. The State-Trait Anxiety Inventory (STAI) [74] is a 40-item measure; 20 items assess for state anxiety and 20 items assess for trait anxiety. Lastly, subsections of the Addiction Severity Index-Lite (ASI-Lite) [83] will be used to assess quantity of substance use in the past 30 days as well as lifetime use patterns.

#### Data management

All electronic data will be stored on encrypted hard drives or password-protected computers. Hard copies of any data will be kept in locked filing cabinets in a secure office. All questionnaire data will be de-identified. An independent data monitoring committee (DMC) will review accumulated data on a regular basis. Additionally, the study’s Institutional Review Board (IRB) will monitor the trial and conduct an audit once per year.

### Data Analysis Plan

Descriptive statistics will be used for demographic information and other baseline characteristics. Our dichotomous primary outcome measure (in attendance/absent) will be compared between oxytocin and placebo treatment conditions using generalized estimating equations to accommodate for correlations among the observations originating from the same participant and correct for interdependence resulting from MIGT cohort membership. Secondary outcomes collected at each MIGT session consist of group cohesion as measured by the GQ, self-reported anxiety as measured by the STAI-6, psychophysiological measures (including heart rate, HF-HRV, and temperature), methamphetamine craving as measured by the MCQ-Br, and urine drug screen. Given the exploratory nature of this novel study design, we will use descriptive statistics and estimate Cohen’s *d* effect sizes for secondary outcomes. Effect sizes will be calculated by subtracting the mean change in the oxytocin group from the mean change in the placebo group and dividing by the pooled baseline standard deviation. If there is substantial missing data, we also will consider using mixed linear models or multiple-imputation techniques to estimate mean change values in each treatment group with greater accuracy. Additional exploratory outcome measures collected at two timepoints, baseline and after the final MIGT session, consist of the SRTB, SPS, IOS, and RTCQ and will be processed using the same methodology. Results of secondary outcomes will be considered exploratory, and further confirmatory studies would be needed to confirm the results. ECR-S, ACE, STAI, and subsections of the ASI-Lite, along with baseline measurements of the SPS, IOS, SRTB, and RTCQ, will be explored as potential predictors of oxytocin response using Pearson’s correlation coefficients.

In addition to utilizing psychophysiology measures recorded during MIGT sessions as a secondary outcome variable in our main data analysis approach, we will utilize models designed to explore physiological synchrony, contagion, and other aspects of shared physiological states [84].

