**Methods/design:**

We are conducting a randomized, double-blind, placebo-controlled trial of oxytocin-enhanced motivational interviewing group therapy (MIGT). Oxytocin or placebo 40 IU is administered intranasally in conjunction with six, weekly MIGT sessions. We will recruit 50 MSM, initiating treatment for MUD from specialized community health programs in San Francisco, CA, USA. Individuals will be randomized (1:1) to receive six, weekly sessions of MIGT with or without oxytocin. Our primary outcome is session attendance. Other outcomes of interest include: measures of group cohesion, anxiety, psychophysiology, and stimulant craving and use.

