Oxytocin administration in combination with evidence-based group psychotherapy—oxytocin-enhanced motivational interviewing group therapy (OE-MIGT)—may synergistically enhance treatment outcomes and address the notoriously high drop-out rates evident in MUD populations. We aim to investigate the effectiveness of intranasally administered oxytocin on MIGT treatment engagement. Specifically, we hypothesize that oxytocin will increase attendance at treatment sessions. In addition, we will estimate effect sizes and assess procedures used to test oxytocin’s effects on group cohesion, anxiety, psychophysiological stress reactivity, and stimulant craving and use for future trials. This novel translational protocol attempts to bridge ample animal data with the need for innovative clinical treatments for MUD.

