## Methods/design

### Study design

This is a randomized, double-blind, placebo-controlled study of OE-MIGT. Specifically, intranasally administered oxytocin or placebo will be administered in conjunction with each of six, weekly, 90-min MIGT sessions.

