### Procedure

Eligible individuals enrolled in the study will be randomized, using a computer-generated random number sequence, to receive MIGT along with either oxytocin or placebo administration prior to each session. Each member of a specific MIGT cohort will receive the same study drug as the other members of that cohort, and members of each MIGT cohort will receive the same study drug for all six sessions. Blinding procedures will be controlled by Wellspring Compounding Pharmacy (Berkeley, CA, USA).

Previous work has shown that intranasal oxytocin administration begins to have physiological effects within 30 min and lasts for at least 90 min [35]. Thirty minutes prior to beginning each MIGT session, the study physician will administer the study drug (Wellspring Compounding Pharmacy, Berkeley, CA, USA) intranasally using a mucosal atomization device (MAD300; Teleflex technologies, Mooresville, NC, USA) attached to a 1-mL Luer-lock syringe. The oxytocin will be prepared as 40 International Units (IU) of oxytocin per 1 mL. Participants will receive 1 mL total, with 0.5 mL administered in each nostril using two separate syringes (with 0.06 mL additional drug in the first syringe to account for the MAD300 dead space). The administration procedures are consistent with recommendations for standardized intranasal drug administration [64]. Study drug administration will occur with all members present in the group therapy space, and the order of administration to individuals within a cohort will be randomized at each session.

To test tolerability to the study drug, participants will complete an Oxytocin Side Effect Checklist (OTSE), a list of 21 possible side effects [37] and the opportunity to report any other adverse effects, after each MIGT session. In addition, participants will be asked after each session to guess whether they have received oxytocin or placebo.

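### Session 1 attendance is settled before the first dose but counts in the primary outcome as written, which dilutes the treatment contrast

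*Protocol article*

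**What the plan says.** The Abstract of the protocol article (Methods/design) fixes the endpoint: "Our primary outcome is session attendance". The Data Analysis Plan scores it as present or absent, with repeated observations per man analysed by generalised estimating equations: "Our dichotomous primary outcome measure (in attendance/absent) will be compared between oxytocin and placebo treatment conditions". The Background gives the hypothesis in the same general terms: "we hypothesize that oxytocin will increase attendance at treatment sessions". The Abstract sets the number of sessions: "Individuals will be randomized (1:1) to receive six, weekly sessions of MIGT with or without oxytocin". No section excludes a session.

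The Procedure section fixes when and where the drug is given: "Thirty minutes prior to beginning each MIGT session, the study physician will administer the study drug", and "Study drug administration will occur with all members present in the group therapy space". No earlier dose is described, and every member of a cohort receives the same study drug throughout. The Study design section adds: "This is a randomized, double-blind, placebo-controlled study of OE-MIGT".

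**The concern.** A man is present or absent at session 1 before he, or anyone in his cohort, has received study drug, and without knowing his arm. The expected treatment effect at that session is zero by design. The earliest attendance that can respond is at session 2, after the session 1 dose. On the plain reading, one of the six scored observations per man therefore carries no treatment effect but is averaged with five that can.

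Two things are at stake. The estimated effect on attendance is smaller than the effect on the sessions that the drug can influence. That matters because the article wants its effect sizes to inform later research (Limitations and future directions). Power may also be lost, in a trial that already expects its group structure to cost power (same section).

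**Working it through.** **Inputs from the protocol article.** Six sessions and 1:1 allocation (Abstract). 25 men per arm, two-sided alpha 0.05, more than 99% power at d = 1.44 and 80% power at d = 0.81 (Power analysis).

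**Assumptions, because the article gives no figure.** Session 1 attendance rate, correlation rho between sessions, and 50% v 78% attendance at sessions 2-6 as an illustration.

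**1. The plan's own figures.** A two-sample t-test with 48 degrees of freedom and noncentrality d × √(25/2) gives 99.9% power at d = 1.44 and 80.1% at d = 0.81. Both stated figures reproduce.

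**2. Attendance difference.** Let Δ be the difference at each of sessions 2-6, with zero at session 1. The unweighted six-session difference is (0 + 5Δ)/6 = 5Δ/6. For 50% v 78%, Δ = 28 points and the six-session difference is 5 × 28/6 = 23.3 points.

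**3. Odds ratio.** At sessions 2-6 it is (0.78/0.22)/(0.50/0.50) = 3.55. Pooled over six sessions, with a share p1 of both arms attending session 1, the arm means are (p1 + 2.5)/6 and (p1 + 3.9)/6:

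| p1 | Arm means | Odds ratio | Shrinkage of log odds ratio |
|---|---|---|---|
| 60% | 51.7% v 75.0% | 2.81 | 18% |
| 80% | 55.0% v 78.3% | 2.96 | 14% |
| 100% | 58.3% v 81.7% | 3.18 | 9% |

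**4. Power when session 1 varies like the other sessions.** With common variance σ² and correlation rho, the mean of k sessions has variance σ²[1 + (k − 1)rho]/k. So the six-session effect is

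d6 = d × √{5(1 + 4rho) / [6(1 + 5rho)]}.

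| rho | Factor | d6 from 0.81 | Power | d6 from 1.44 | Power |
|---|---|---|---|---|---|
| 0 | 0.913 | 0.739 | 72.6% | 1.315 | 99.5% |
| 0.4 | 0.850 | 0.688 | 66.5% | 1.224 | 98.9% |
| 1 | 0.833 | 0.675 | 64.8% | 1.200 | 98.6% |

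Scoring sessions 2-6 only, power is 80.1% and 99.9%. The largest losses are 80.1 − 64.8 = 15.3 points and 99.9 − 98.6 = 1.3 points.

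**5. Power when everyone attends session 1.** The mean difference and its standard deviation both shrink by 5/6, so d and power do not change.

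**6. Between these cases.** Correlated binary attendance was simulated with 50% v 78% at sessions 2-6, latent correlation 0.6 and 20,000 trials per scenario, comparing each man's attendance fraction by t-test:

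| Session 1 attendance | Power, all six | Power, sessions 2-6 |
|---|---|---|
| 60% | 69% | 82% |
| 80% | 72% | 82% |
| 90% | 76% | 83% |
| 97% | 80% | 82% |
| 100% | 82% | 82% |

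**7. With clustering.** A second simulation used ten cohorts of five, a log-odds effect of 1.7 on sessions 2-6 only, participant variance 1 or 3, cohort variance 0 or 0.3, and a t-test on cohort means. With 50% attending session 1, power for all six v sessions 2-6 was about 88 v 95, 65 v 79, 56 v 71 and 46 v 58. With 92-96% attending, the loss was about 1 to 5 points. With 99% or more, it was 1 point or less.

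**The case against.** The strongest reply is that no sentence says session 1 is scored, how sessions are weighted, or whether the model has session terms. A fuller protocol or analysis plan could leave session 1 out. That stands as a limit: counting session 1 is the plain reading, not an explicit statement. It does not remove the point, because the outcome is defined here as attendance over six sessions without exception, and that definition includes a pre-dose observation.

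Second, the men have passed a telephone screen and an in-person assessment and have consented, so nearly all may attend session 1. If so, almost no power is lost. This also stands. The attenuation of the attendance difference and odds ratio remains even then.

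Third, attendance over the whole programme is a legitimate intention-to-treat target that matches the stated hypothesis, and the comparison is unbiased for it. This is right. A reader might infer that the result is biased toward the null, but dilution is the correct word: the sessions 2-6 endpoint answers a different question.

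Other stronger readings are also unsupported:
- **The stated power is wrong.** The figures reproduce. The pilot d of 1.44 may already include that trial's first session; the article does not say.
- **The effect shrinks by exactly one sixth.** That holds for the unweighted attendance difference, not for the odds ratio that a generalised estimating equation with a logit link would report.
- **A large power loss is certain.** Losses of 7 to 15 points in the clustered simulation need about half the men to miss session 1.
- **Drop-out while waiting for a cohort to start adds noise.** The article does not describe this, and such men would be scored absent at sessions 2-6 too.

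**Conclusion.** The point holds as one of dilution. Under the double blind and on-site dosing, session 1 attendance cannot respond to study drug, so including it reduces the six-session attendance difference to 5/6 of the sessions 2-6 difference and attenuates the odds ratio (from 3.55 to between 2.81 and 3.18 in the illustration).

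The effect on power is conditional. For a true d of 0.81 on sessions 2-6, power falls from 80% to 65-73% if session 1 varies like the other sessions, and hardly at all if nearly everyone attends. At d = 1.44 the loss is at most about 1.3 points. These figures ignore cohort clustering, which would lower every power value. They rest on assumed session 1 attendance and correlation and on a t-test of attendance fractions, not on the planned model.

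The dilution does not favour oxytocin and does not raise the type I error. The change is worth making because it is nearly free, not because the analysis is invalid as it stands.

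**What to change.** Before unblinding, define the primary outcome as attendance (yes/no) at sessions 2-6 in all randomised men, analysed with the planned generalised estimating equations. Report session 1 attendance by arm as a pre-dose check of balance, and optionally include it as a covariate. Keep attendance over all six sessions as a sensitivity analysis. If a fuller protocol or analysis plan already excludes session 1, state this alongside the outcome definition.

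The cost is a change of wording and no new data. The endpoint has five observations per man instead of six and no longer describes attendance over the whole programme; the sensitivity analysis supplies that. A man who misses session 1 is still undosed when session 2 attendance is decided. He should stay in the analysis, so the new endpoint removes the structural zero but not every undosed observation.

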The MIGT cohorts in this study will consist of two co-facilitators, one will be a licensed psychiatrist and the other will be a mental health trainee (PhD, PsyD, or psychiatry resident) along with four to six group members. All MIGT sessions will be conducted at the Alliance Health Project in San Francisco, CA, USA. A semi-structured, closed-admission, time-limited (six sessions) OE-MIGT manual for methamphetamine users was developed for this study using guidance from Wagner and Ingersoll (2013) [55]. Included are four brief psychoeducational components for optional use during the first four sessions: stages of change, ambivalence and a decisional balance chart for methamphetamine use, attachment theory and social support, and managing stress. These topics aid in the Engagement and Exploring Perspectives phases of the group, are designed to maximize the effects of intranasally administered oxytocin on MIGT for MUD, and correspond to the specific objectives of this research study. The final two sessions are left unstructured in order to allow more time for Broadening Perspectives and Moving Into Action. Adherence raters will assess session transcripts using motivational interviewing treatment integrity (MITI) 4.2; a coding system designed to measure group facilitators’ adherence to MI [56]. Consistent with previous work by the research team, a fidelity checklist reflecting the content of the session will be developed in order to determine whether the intervention was delivered as intended. Prior to participant enrollment, facilitators will receive training from an MI expert to ensure competency [57, 58].

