### Setting and study population

Previous evidence suggests that oxytocin administration may lead to different outcomes based on the gender [59] and sexual orientation [60] of recipients. To control for this, we limited study participation to men who have sex with men (MSM). Fifty MSM who meet the criteria for MUD will be enrolled in the current study. Participants will be recruited from community mental health programs specializing in this clinical population in San Francisco, CA, USA, including the San Francisco AIDS Foundation, the Alliance Health Project, the Positive Health Program HIV/AIDS Clinic, as well as from study flyers posted in the community. Due to the specificity of our patient population, we acknowledge that participants may recognize each other or even belong to the same social circles. While we do not formally measure pre-existing relationships among those assigned to the same therapy cohort, we do take steps to ensure that intimate partners are not assigned to the same therapy cohort by collecting names of intimate partners as well as any community member that each potential participant would *not* want to be enrolled with in group therapy.

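### The primary GEE test rests on only about 10 to 12 therapy cohorts, so unless a small-sample correction is prespecified its two-sided error is about 10-12%, not 5%

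*Protocol article*

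**What the plan says.** The Data Analysis Plan section of the protocol article fixes the primary comparison. Attendance at each session, yes or no, is to be analysed by "generalized estimating equations to accommodate for correlations among the observations originating from the same participant and correct for interdependence"; the interdependence meant is the one that arises from sharing a therapy cohort. The section names no variance estimator, working correlation, reference distribution or small-sample correction, and it rules none out.

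Three other statements determine how many independent units that analysis has:

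- Procedure: "Each member of a specific MIGT cohort will receive the same study drug as the other members of that cohort". The assigned drug does not change over the six sessions.
- Motivational interviewing group therapy (MIGT): a cohort consists of two co-facilitators "along with four to six group members".
- Setting and study population: "Fifty MSM who meet the criteria for MUD will be enrolled in the current study". The Power analysis section puts 25 in each condition, with a two-tailed alpha of 0.05.

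The Limitations section says that the complications of group therapy for the analysis will be taken into account, probably at a cost in power. It does not mention the type I error.

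**The concern.** GEE inference is justified when there are many independent clusters. To correct for cohort membership, the cohort must be the cluster, and the design yields about a dozen at most. With so few, the usual sandwich variance is too small on average and the normal reference distribution is too narrow. Both faults push toward too many rejections.

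The consequence is serious because attendance is the trial's only hypothesis test; the same section treats all secondary outcomes as exploratory and summarises them with effect sizes. If the error rate is about double the stated 5%, a p-value just under 0.05 is weak evidence and the confidence interval covers less often than it claims. The Limitations section expects clustering to cost power. Uncorrected GEE would err the other way, toward false positives.

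**Working it through.** **Inputs from the article.** 50 men, 25 per arm; 4 to 6 per cohort; one drug per cohort; 6 sessions; binary attendance at each session; two-sided alpha 0.05.

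**The article's own figures.** A two-sample t calculation with 25 independent men per arm gives power of 99.9% at d = 1.44 and 80.1% at d = 0.81. This matches the stated values of more than 99% and 80%, so the power calculation treats the 50 men as independent.

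**Number of cohorts, K.**

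- Per arm: 25/6 = 4.2, so at least 5; 25/4 = 6.25, so at most 6. Hence K = 10 to 12.
- If the arms need not be exactly 25: 50/6 = 8.3, so at least 9; 50/4 = 12.5, so at most 12.

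**Size of the uncorrected test.** With equal arms and equal cohorts, the uncorrected sandwich variance is too small on average by the factor (K−2)/K, and the Wald statistic behaves like t on K−2 df multiplied by √(K/(K−2)). Testing it against 1.96 gives

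size = 2 × P(t on K−2 df > 1.96 × √((K−2)/K)).

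| K | effective cut-off | size |
|---|---|---|
| 9 (approximate, arms unequal) | 1.96 × √(7/9) = 1.729 | 12.8% |
| 10 | 1.96 × √(8/10) = 1.753 | 11.8% |
| 12 | 1.96 × √(10/12) = 1.789 | 10.4% |

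The formula contains no intracluster correlation (ICC), so the inflation remains when the cohort ICC is 0.

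**Check by simulation.** Logistic GEE, cohort as cluster, independence working correlation, 20,000 replicates per setting. Assumed, because the article gives no values: attendance 50% or 70%, cohort ICC 0 to 0.2, participant ICC 0.4 on the latent scale. Size was 12.1-12.9% at 9 cohorts, 10.6-11.9% at 10 and 9.4-10.6% at 12. Unequal cohorts (4, 4, 5, 6, 6 per arm) gave 11.4-11.9%.

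**Length of the interval.** In the balanced case the correct multiplier of the uncorrected standard error is t(0.975, K−2) × √(K/(K−2)).

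- K = 10: 2.306 × 1.118 = 2.578. The uncorrected interval has 1.96/2.578 = 76% of the proper length and covers 100 − 11.8 = 88.2%.
- K = 12: 2.228 × 1.095 = 2.441. It has 1.96/2.441 = 80% of the proper length and covers 100 − 10.4 = 89.6%.

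**With the correction.** Kauermann-Carroll scales each cluster residual by the inverse square root of (1 − leverage). In the balanced case with K/2 cohorts per arm, leverage is 2/K, so the variance is multiplied by 1/(1 − 2/K) = K/(K−2). That is exactly the missing factor, and a t reference on K−2 df then restores the nominal level. In simulation this test rejected a true null about 4-5% of the time.

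**The case against.** The strongest objection is that the faulted procedure is not in the text. The article names GEE and promises to correct for cohort membership. It does not say that the sandwich variance is uncorrected or that the reference is normal, and such details are commonly left to an analysis plan, which is not shown. This stands as far as it goes: 10-12% cannot be stated as the error rate of the trial's test, only as the rate if the standard robust Wald test is used. It does not dispose of the point. The article fixes a large-sample method for a design with 10 to 12 treatment-carrying units, and the method in its standard form gives the wrong error rate.

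Two stronger readings are tempting, and the article does not support them.

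- A reader might infer that GEE fails whichever cluster is chosen, since clustering on the participant alone would also inflate the error (5.5-5.9% at cohort ICC 0, 15.5-22.4% at an assumed 0.2). But the Data Analysis Plan says that cohort membership will be corrected for, so participant-only clustering would contradict it. Cohort-clustered GEE with a suitable correction does hold its level.
- A reader might infer an error as high as 13-14%. That needs 8 cohorts, which hold at most 8 × 6 = 48 men, fewer than the 50 planned. It could arise only if recruitment fell short.

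The general promise in the Limitations section to take grouping into account shows awareness of clustering. It names no method and mentions no risk to the type I error.

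**Conclusion.** The concern holds in conditional form. The planned numbers give 5 or 6 cohorts per arm. If the primary GEE is run with the cohort as cluster and the standard robust Wald test against the normal distribution, the two-sided size is about 10-12% instead of 5%, and up to 12.8% if there are only 9 cohorts. The 95% interval is then about 20-24% shorter than it should be.

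The cohort count and the dependence of treatment on cohort come from the article. The analytic sizes assume equal arms and cohort sizes and roughly normal cohort means. The simulations relax this, at assumed attendance rates and ICCs, and agree. The inflation does not depend on any assumed strength of cohort correlation. What remains unknown is whether an unshown document already specifies a correction; if it does, the point is met.

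**What to change.** State in the analysis plan, before unblinding:

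1. The cohort is the GEE cluster, with participants and their sessions nested in it.
2. The primary p-value and confidence interval use a Kauermann-Carroll corrected sandwich variance (cluster residuals scaled by the inverse square root of 1 minus leverage), with a t reference on the number of cohorts minus 2 df. The scaling should be written out: the full inverse is the Mancl-DeRouen correction, which with the same t reference gave 2.7-3.5% and is conservative here.
3. As a sensitivity analysis, a permutation test of treatment labels across cohorts, following the way labels were actually assigned. With 5 v 5 cohorts the smallest two-sided p-value is 2/252 = 0.008, so significance at 5% is attainable.
4. The cohort ICC is reported.

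The change takes a few sentences and a software option, with no new data. The interval becomes wider than the uncorrected one: by 2.578/1.96 = 1.32 times at 10 cohorts and 2.441/1.96 = 1.25 times at 12. Power also falls below the stated figure. With a t reference on K−2 df and an assumed cohort ICC of 0.01 to 0.1, power at d = 0.81 is about 57-69% with 10 cohorts and 62-72% with 12, against the stated 80%. Part of that loss comes from the clustering itself and would exist under any valid test.

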### Power analysis

A sample size of 25 per treatment condition will provide us with > 99% power to detect an effect size comparable to the large between-condition effect size (*d* = 1.44) observed for attendance from our preliminary 3-week trial in cocaine users [53] with a two-tailed alpha = 0.05. In addition, this sample size will provide 80% power to detect an effect size of 0.81 or greater.

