#### Substance use data collection

A urine sample will be collected at each study visit. A point-of-care, Clinical Laboratory Improvement Amendments (CLIA)-waived, 10-panel, Toxicology iCup Dx drug screen (Alere Inc., Waltham, MA, USA) will be used to screen samples for methamphetamine and other common substances of abuse.

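### The urine drug screen, naturally a positive/negative result, falls under a Cohen's d rule whose denominator is set by baseline prevalence alone; a risk difference would serve the trial's aim better

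*Protocol article*

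**What the plan says.** The Data Analysis Plan of the protocol article lists the secondary outcomes taken at each session: group cohesion, anxiety, psychophysiology and, last, "methamphetamine craving as measured by the MCQ-Br, and urine drug screen". For this set it states that "we will use descriptive statistics and estimate Cohen’s *d* effect sizes for secondary outcomes". The effect size is the placebo mean change minus the oxytocin mean change, formed by "dividing by the pooled baseline standard deviation". No outcome is exempted.

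Under Substance use data collection, the urine test is a point-of-care 10-panel device, applied to a sample at each study visit, that "will be used to screen samples for methamphetamine and other common substances of abuse". No concentration or other quantitative reading is mentioned.

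The same Data Analysis Plan calls attendance dichotomous and gives it generalized estimating equations (GEE), with allowance for repeated observations and cohort membership. The Background section says that effect sizes for stimulant craving and use, among other outcomes, are being estimated for future trials.

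**The concern.** Cohen's d is meant for a roughly continuous measure whose spread is a property separate from its mean. A 0/1 result has no separate spread: once the proportion positive is known, so is the SD. Dividing by the baseline SD therefore rescales the treatment effect by a function of baseline prevalence. Two trials with the same absolute effect on positivity would report different values of d because they enrolled men at different points in their use, and d grows without limit as baseline positivity approaches 100%.

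This matters because the secondary effect sizes are meant to inform later trials. A planner who took the d for urine results at face value could not tell how much of it was treatment effect and how much was the baseline rate. The plan already contains a suitable approach for a binary outcome but applies it only to attendance.

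**Working it through.** **The plan's own figure.** The Power analysis section says "A sample size of 25 per treatment condition will provide us with > 99% power" for d = 1.44, "with a two-tailed alpha = 0.05", and that "this sample size will provide 80% power to detect an effect size of 0.81 or greater". A two-sample t-test calculation with 25 per arm gives 99.9% power at d = 1.44 and 80.1% at d = 0.81, so both statements reproduce. They concern attendance. No power is stated for the urine screen, and the present point does not depend on these figures.

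**Inputs**
- Effect size rule: (mean change on placebo − mean change on oxytocin) / pooled baseline SD, from the Data Analysis Plan.
- Urine result coded 1 = positive, 0 = negative. This is inferred from the description of the device; the article does not say it in words.
- Baseline proportion positive, p: not given, so varied from 50% to 100%.
- Illustrative effect, assumed: positivity falls 10 points on placebo and 30 points on oxytocin. The numerator is then (−0.10) − (−0.30) = 0.20.

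**Formula.** For a 0/1 variable, SD = sqrt(p(1 − p)), so d = 0.20 / sqrt(p(1 − p)).

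| Baseline positive, p | SD | d | Risk difference |
|---|---|---|---|
| 50% | 0.500 | 0.40 | 0.20 |
| 80% | 0.400 | 0.50 | 0.20 |
| 90% | 0.300 | 0.67 | 0.20 |
| 95% | 0.218 | 0.92 | 0.20 |
| 100% | 0 | undefined | 0.20 |

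The risk difference is constant because the example holds it fixed. The table shows how far d moves when the absolute effect does not. Using the sample SD for 50 men (variance multiplied by 50/49) changes little: 0.40, 0.49 and 0.66 at 50%, 80% and 90%.

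**Chance variation in the denominator.** With 50 baseline samples the observed p varies. In a simulation with a true rate of 90% and the numerator held at 0.20, the central 95% of d ran from about 0.52 to 1.41. At a true rate of 95%, the chance that all 50 samples are positive, so that d cannot be computed, is 0.95^50 = 0.077, or about 8%. At 90% it is 0.90^50 = 0.005.

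**The odds ratio.** In the same example, the odds of a positive final result on placebo relative to oxytocin range from about 2.3 to 3.9 as p goes from 50% to 100%. The odds ratio also depends on baseline, but it stays finite here.

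**The case against.** Several points on the other side stand.

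- Descriptive statistics are planned alongside d. For a positive/negative screen these would probably include percentages by arm, which a later trial could use. A reader might infer that the trial will yield nothing usable on methamphetamine use; the article does not support that. What stands is that d is the only between-arm measure it names for this outcome.
- High baseline positivity is an assumption. Severe methamphetamine use disorder is required, but men who began treatment within the past month are eligible and some may be abstinent. Between 50% and 80%, d moves only from 0.40 to 0.50. The extreme values need 95% or more, and nothing in the article establishes such a rate.
- Secondary results are labelled exploratory and in need of confirmation. No primary inference is affected.
- Missing data are not ignored: mixed linear models or multiple imputation will be considered if the loss is substantial. These would estimate the mean changes better but leave the same denominator.

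A stronger reading is also tempting on self-report: that the Timeline Follow Back (TLFB), which records use over the past 7 days, is collected and never analysed. It is indeed absent from the outcome and predictor lists in the Data Analysis Plan. But this is a condensed article, and a full protocol or SAP that is not shown may place it. Its timing is in a figure that is not shown. Use as an outcome is already represented by the urine screen, and the Addiction Severity Index-Lite quantifies past-30-day use at screening. The omission is worth a query to the sponsor but is not an established fault.

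**Conclusion.** The point holds for the urine screen. The stated rule covers it without exception, and for a 0/1 result that rule gives an effect size governed by an unreported baseline rate: from 0.40 to 0.92 for one and the same 20-point difference as baseline positivity goes from 50% to 95%, and no value at 100%. This rests on reading the screen as positive/negative and on an assumed range of baseline rates.

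The consequence is small. It concerns one exploratory outcome and the usefulness of its effect size for planning. The primary outcome, the sample size and the continuous secondary outcomes are unaffected. The change is worth making because it costs almost nothing.

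**What to change.** - Exempt the urine screen from the Cohen's d rule. Report the proportion positive for methamphetamine by arm and session, with a between-arm risk difference and confidence interval that allows for repeated samples from a man and for cohort membership, as already planned for attendance.
- Add an odds ratio only if it is stable. With 50 men in groups of four to six there will be roughly 8 to 13 cohorts (50/6 = 8.3; 50/4 = 12.5), and a positivity rate near 100% would make the estimate fragile.
- State the number of samples obtained per arm and session. Samples come only from men who attend, and attendance is what oxytocin is expected to change.
- Keep any analysis that counts a missed sample as positive as a sensitivity analysis, with a note that it mixes the attendance effect into the use outcome.
- When the wording is revised, confirm where the TLFB is analysed.

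The cost is a few lines in the analysis plan. The urine changes need no new data and no change to conduct or sample size.
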